A parallel two-arm RCT will be undertaken to determine if aerobic exercise is an effective strategy to prevent and/or mitigate CRCC and its impact on quality of life among women who receive chemotherapy for breast cancer. The primary objective of the Aerobic exercise and CogniTIVe functioning in women with breAsT cancEr (ACTIVATE) trial is to test the effect of an aerobic exercise intervention initiated during chemotherapy (EX) compared to a usual care wait-list control group (exercise initiated post-chemotherapy; UC) on objectively measured cognitive functioning in women who receive chemotherapy for breast cancer. Secondary objectives are to: (1) test the effects of EX compared to UC on (a) self-reported cognitive functioning, (b) global and regional measures of brain structure and functioning with magnetic resonance imaging (MRI) and functional MRI (fMRI) focussing on areas underlying attention and working memory, and (c) overall global and regional brain network organization and neural functioning in areas underlying attention and working memory using electroencephalography (EEG), and; (2) assess if the timing of the intervention (i.e., during versus post-chemotherapy) moderates the effects of exercise. It is hypothesized that: (1) the EX group will perform better on neuropsychological tests (primary outcome) than the UC group post-chemotherapy (primary endpoint) and at other timepoints; (2) the EX group will maintain pre-chemotherapy brain structure and functioning post-chemotherapy and at other timepoints whereas the UC group will have significant changes in both, and; (3) the EX group will self-report better cognitive functioning and psychosocial outcomes (i.e., quality of life, psychological health, cancer-related fatigue) post-chemotherapy and at other timepoints compared to the UC group.

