#### The ACTIVATE intervention (EX condition)

The ACTIVATE intervention is delivered concurrently with participants’ chemotherapy regimen (starting up to 1 week before participants’ chemotherapy start date and lasting approximately 12–24 weeks for those in the EX group). Tables 1 and 2 provide an overview of the progressive aerobic exercise prescription. The intervention is based on prior protocols used by the study team for women receiving treatment for breast cancer or who have completed treatment for breast cancer [56–59]. Participants complete three supervised aerobic exercise sessions each week at the Breast Cancer Training Center or at the Chan Gunn Pavilion on the University of British Columbia campus for the Vancouver site, or at the University of Ottawa Behavioural and Metabolic Research Unit for the Ottawa site. Supervision of the exercise sessions is provided by trained exercise professionals who have a valid CPR-C certification and experience supervising exercise in chronic disease populations.

**Table 1 Tab1:** Details of supervised and home-based exercise prescription for participants on a 3-week chemotherapy cycle protocol

Cycle	Week	Supervised Program			Home-based Program		
		Freq.	Duration (minutes)	Intensity (% HRR)	Freq.	Duration (minutes)	Intensity (RPE)
1	1	3	20–25	50–55^a^, 55–60	0	0	0
	2	3	30	55–60	0	0	0
	3	3	25–30	60–65	1	15–20	12–13
2	4	3	30–35	50–55^a^, 60–65	1	15–20	12–13
	5	3	25–35	60–65, VT	1	15–20	12–13
	6	3	25–35	60–65, VT	1	20–30	12–13
3	7	3	35–40	55–60^a^, 60–65	1	20–30	12–13
	8	3	25–35	65–70, VT	1	20–30	12–13
	9	3	25–35	65–70, VT	1	20–30	12–13
4	10	3	35–40	55–60^a^, 65–70	1	20–30	12–13
	11	3	20–35	65–70, HIIT	1	20–30	12–13
	12	3	20–40	65–70, HIIT	1	20–30	12–13
5	13	3	40	55–60^a^, 65–70	1	20–30	12–13
	14	3	20–35	70–75, VT/HIIT^b^	1	20–30	12–13
	15	3	20–35	70–75, VT/HIIT^b^	1	20–30	12–13
6	16	3	40	55–60^a^, 65–70	1	20–30	12–13
	17	3	20–35	70–75, VT/HIIT^b^	1	20–30	12–13
	18	3	20–35	70–75, VT/HIIT^b^	1	20–30	12–13
7	19	3	40	55–60^a^, 65–70	1	20–30	12–13
	20	3	20–35	70–75, VT/HIIT^b^	1	20–30	12–13
	21	3	20–35	70–75, VT/HIIT^b^	1	20–30	12–13
8	22	3	40	55–60^a^, 65–70	1	20–30	12–13
	23	3	20–35	70–75, VT/HIIT^b^	1	20–30	12–13
	24	3	20–35	70–75, VT/HIIT^b^	1	20–30	12–13

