
#### Comparison condition: usual care wait-list control (UC)

Participants who are allocated to the UC condition receive the ACTIVATE intervention for approximately 12 weeks following their last chemotherapy infusion. They are advised to continue with their regular activities of daily living during chemotherapy. No exercise restrictions are made.

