### Data collection

#### Primary outcome

##### Objective assessment of cognitive functioning

At four of the five study timepoints (i.e., baseline (pre-intervention), end of chemotherapy (post-intervention/post-wait period; primary endpoint), 16-weeks post-chemotherapy (first follow-up), and at 1-year post-baseline (second follow-up)), participants complete a neuropsychological test battery that is used to compute a composite cognitive summary score (COGSUM). The battery covers verbal and visual memory, attention/working memory, and processing speed, and was chosen because these cognitive domains have been shown to be sensitive to adverse effects of chemotherapy in previous studies [54]. Moreover, the specific tests were chosen because they have accounted for most of the between-group variance observed with a larger test battery [54]. The order of tests is as follows: Hopkins Verbal Learning Test Revised (verbal memory [63]), Brief Visuospatial Memory Test Revised (visual memory [64]), Weschler Adult Intelligence Scale-IV (WAIS-IV) Digit-Symbol Coding (processing speed [65]), WAIS-IV Letter-Number-Sequencing (working memory [65]), Auditory Consonant Trigrams Test (working memory [66]), Controlled Oral Word Association Test (working memory [67]), and Trail Making Test A and B (processing speed and cognitive flexibility/task switching capacity [68]). To reduce practice effects, different testing forms are used at each timepoint, with the exception of the WAIS-IV tests, Controlled Oral Word Association Test, and Trail Making Tests A and B, where alternate forms are not available.

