### Statistical analyses

Descriptive statistics will be computed for baseline socio-demographic and medical characteristics. Baseline socio-demographic and medical characteristics will be compared between participants who have completed assessments and those who dropped out in order to assess for attrition bias. Characteristics commonly associated with attrition (e.g., age, length of chemotherapy) will be included as covariates in all analyses under the assumption of “missing at random”. Analyses will be on an intent-to-treat basis, with per-protocol analyses considered as exploratory.

The primary outcome (i.e., cognitive functioning as indexed by COGSUM scores) will be analyzed using repeated measures ANOVA with fixed terms for time and a treatment by time interaction (constrained baseline differences). The stratification factors (i.e., study site and menopausal status) as well as factors associated with attrition (e.g., age and length of chemotherapy) will be included as covariates in the analyses. Correlation in repeated measures on the same individual over time will be accounted for by explicitly modeling the covariance matrix, with the best-fitting covariance structure decided using likelihood ratio tests and information criteria. The difference between the EX and UC groups at end of chemotherapy (primary comparison) will be calculated as adjusted least square mean difference in change from baseline, together with 95% confidence intervals. 

To test the effect of timing of the aerobic exercise (i.e., during versus post-chemotherapy) on outcomes at 1-year post-baseline, the models as described above will additionally include the response at 1-year follow-up and the contrast of interest will be the difference in change from baseline to 1-year after the start of chemotherapy. The sustainability of the intervention will be examined in each group by testing the change in response from immediately post-chemotherapy (post-intervention/post-wait period) to 1-year post-baseline, together with a 95% confidence interval.

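### No contrast is named at the 16-week post-chemotherapy visit, the only cognitive visit soon after the wait-list arm's exercise, and the plan does not say that this visit enters the model

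*Protocol article*

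**What the plan says.** **Visits.** Under Objective assessment of cognitive functioning, the battery behind COGSUM is given "At four of the five study timepoints (i.e., baseline (pre-intervention), end of chemotherapy (post-intervention/post-wait period; primary endpoint), 16-weeks post-chemotherapy (first follow-up" and again at 1 year after baseline. Self-reported cognition and the other questionnaires are collected at all five visits, so 16 weeks is included for them too.

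**Exercise periods.** The EX programme runs alongside chemotherapy, "lasting approximately 12–24 weeks for those in the EX group". UC participants "receive the ACTIVATE intervention for approximately 12 weeks following their last chemotherapy infusion".

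**Objectives.** The Background sets as secondary objective 2 to "assess if the timing of the intervention (i.e., during versus post-chemotherapy) moderates the effects of exercise". Its hypotheses 1 and 3 expect EX to do better after chemotherapy and also at the other timepoints.

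**Analysis.** Under Statistical analyses, COGSUM "will be analyzed using repeated measures ANOVA with fixed terms for time and a treatment by time interaction (constrained baseline differences"). The visits in that model are not listed. Three COGSUM comparisons are named:

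1. The primary one: "The difference between the EX and UC groups at end of chemotherapy (primary comparison) will be calculated as adjusted least square mean difference", where each arm's result is its change from baseline.
2. For timing, "the models as described above will additionally include the response at 1-year follow-up", and the contrast is EX versus UC in change from baseline to 1 year.
3. For sustainability, the change within each arm from end of chemotherapy to 1 year.

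For the secondary outcomes the contrast stated is EX versus UC after chemotherapy. Nowhere in the section is the 16-week visit mentioned.

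**The concern.** For UC, the end-of-chemotherapy and 16-week visits bracket the exercise programme: one lies before it and the other shortly after. That makes 16 weeks the visit at which an effect of exercise started after chemotherapy should be easiest to see. The plan collects a full battery there and then names no use for it.

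Three things follow.

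- The timing objective is answered only at 1 year, when the UC programme has been over for months and any effect may have faded.
- The hypotheses about other timepoints have no stated 16-week estimate. If one is reported later, it will look as though it was chosen after seeing the data.
- The sustainability comparison does not mean the same thing in the two arms. In EX it starts when the programme has just ended, so it does measure whether a gain lasts. In UC it starts at the end of the waiting period, before any trial exercise, so it adds the gain during the programme to whatever is lost afterwards. A UC change near zero could be no gain at all, or a gain followed by an equal loss.

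**Working it through.** **1. Timeline.** Inputs: chemotherapy of about 12 to 24 weeks (EX condition section), UC exercise for about 12 weeks after the last infusion (Comparison condition section), visits at 16 weeks after chemotherapy and 1 year after baseline. I take baseline as the start of chemotherapy and 1 year as 52 weeks, and assume that UC starts exercise promptly.

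| Chemotherapy length (weeks) | UC exercise ends (week) | 16-week visit (week) | Gap to 16-week visit | Gap to 1-year visit | End of chemotherapy to 1 year |
|---|---|---|---|---|---|
| 12 | 24 | 28 | 4 | 28 | 40 |
| 16 | 28 | 32 | 4 | 24 | 36 |
| 24 | 36 | 40 | 4 | 16 | 28 |

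The UC sustainability window is therefore 28 to 40 weeks long, of which about 12 are exercise: 12/40 = 30% to 12/28 = 43%.

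**2. The plan's own sample size.** Inputs from the Sample size section: 0.4 SD, correlation with baseline 0.8, two-sided 5%, 80% power, ANCOVA. Residual SD = √(1 − 0.8²) = 0.6. Noncentral t with 2n − 3 degrees of freedom gives 79.6% at 36 per arm and 80.7% at 37 per arm, so 74 in total. With 10% dropout, 74/0.9 = 82.2, which rounds up to 83 and to 84 for equal arms. The stated 74 and 84 reproduce, and nothing below changes them.

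**3. What the 16-week data could deliver.** Assume 37 per arm and the same SD at each visit. The correlation between end of chemotherapy and 16 weeks is not in the document, so I vary it.

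The difference between arms in change from end of chemotherapy to 16 weeks has SD of change √(2(1 − r)) and SE = SD × √(2/37). At r = 0.8 the SD is 0.632 and the SE is 0.632 × 0.2325 = 0.147. Power uses noncentral t with 72 degrees of freedom.

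| r | SE (SD units) | 95% CI half-width | Power, 0.4 SD | Power, 0.2 SD |
|---|---|---|---|---|
| 0.7 | 0.180 | 0.36 | 59% | 19% |
| 0.8 | 0.147 | 0.29 | 77% | 27% |
| 0.9 | 0.104 | 0.21 | 97% | 48% |

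A 0.4 SD change means that a gap equal to the whole minimum important difference closes completely. The 0.2 SD column is half closure.

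For the baseline-adjusted EX-UC difference at 16 weeks, the difference detectable with 80% power is 2.80 × √(1 − r²) × √(2/37), where r is now the correlation with baseline. That is 0.39 SD at 0.8, and 0.28 to 0.52 SD over r = 0.9 to 0.6.

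**4. What a 16-week contrast means.** From end of chemotherapy to 16 weeks, UC is on and then just past its programme, and EX is past its own. Recovery and practice effects that are common to both arms cancel in the randomised difference in change. What remains is UC gain plus any EX fading. No arm is left without exercise, so these two cannot be separated by design.

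**The case against.** The strongest case on the other side has four parts.

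**The visit may already be in the model.** A reader might infer from the section that the 16-week data are excluded. The document does not establish that. COGSUM is not measured mid-chemotherapy, so a base model without 16 weeks would hold only two visits, and choosing a covariance structure by likelihood ratio tests would then have little purpose. A base model with the 16-week visit, to which the 1-year response is added, is a natural reading. This stands. It leaves the inclusion unclear and still gives no named 16-week contrast.

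**A condensed article may leave such detail elsewhere.** This is fair for a list of model visits. But the article does define its timing contrast and its sustainability window, and those choices can be judged as written.

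**Post-chemotherapy exercise is not wholly unassessed.** It would be tempting to say that the trial never estimates its effect. That goes too far. The 1-year contrast is a randomised comparison of exercise during with exercise after chemotherapy, and the within-UC change to 1 year spans the UC programme. Both are late, and the second is uncontrolled, but they are estimates.

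**A 1-year difference near zero is not uninterpretable.** A reader might infer that only a 16-week contrast can tell UC catch-up from no effect of either programme. It is not so: if neither programme worked, no gap is expected at end of chemotherapy either, so the primary and 1-year contrasts read together already address this. Nor would a 16-week contrast isolate the effect of post-chemotherapy exercise, because a narrowing gap could equally be EX losing ground.

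What survives is a gap in what the plan names, and a sustainability measure that starts at the wrong visit for UC.

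**Conclusion.** The point holds in a limited form. The analysis section names no contrast at 16 weeks and does not say that this visit enters the model, although it is the only cognitive visit soon after the UC programme: about 4 weeks after it, against about 16 to 28 weeks at 1 year. The timing objective therefore rests on the 1-year contrast alone, the hypotheses about other timepoints lack a 16-week estimate, and the UC sustainability change mixes gain with loss.

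The primary comparison and the sample size are unaffected. The intervals in weeks rest on the approximate programme lengths in the article. The precision figures rest on 37 analysed per arm and a between-visit correlation that the article does not give. With that correlation at 0.8, full closure of a 0.4 SD gap would be detected with about 77% power, but half closure with only about 27%. The added estimates are thus worth having as closer-in-time descriptions with intervals; they are not a second confirmatory test.

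**What to change.** - State the visits in the model: one constrained-baseline repeated measures model on all four COGSUM visits, and on all visits for the questionnaires.
- Keep EX-UC at end of chemotherapy as the primary contrast and EX-UC at 1 year as planned.
- Add two secondary estimates with 95% confidence intervals: the EX-UC difference at 16 weeks, and the EX-UC difference in change from end of chemotherapy to 16 weeks. Label the second as combining UC gain with any EX fading, because no arm is unexercised.
- Measure sustainability in UC from 16 weeks to 1 year, and in EX from end of chemotherapy to 1 year as now. Note that the two windows differ in length.

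The cost is analysis-plan wording and a few more secondary estimates to report. It needs no new participants, visits or tests. The change should be made before the allocation is unblinded. The report should say that power for partial closure of the gap is low, so that a wide interval is not read as evidence of no effect.

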### Study design

The ACTIVATE trial is a two-arm, two-centre, single-blinded parallel group RCT. After completing a baseline (pre-chemotherapy) assessment, recruited women are randomized to one of two groups: (1) exercise condition in which they receive an aerobic exercise intervention during chemotherapy (EX), or; (2) usual care wait-list control condition in which they receive usual care during chemotherapy and an aerobic exercise intervention after completing chemotherapy (UC). Additional assessments take place mid-way through chemotherapy (mid-intervention/mid-wait period), post-chemotherapy (post-intervention/post-wait period), 16-weeks post-chemotherapy (first follow-up), and at 1-year post-baseline (second follow-up). Figures 1 and 2 summarize the ACTIVATE trial design and the process of randomization, group allocation, and assessment timepoints.

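### The sustainability analysis starts the usual-care (UC) arm at a visit before it has received the ACTIVATE programme, so the UC result does not measure sustainability

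*Protocol article*

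**What the plan says.** The last sentence of the primary-outcome text under Statistical analyses says that the "sustainability of the intervention will be examined in each group by testing the change in response from immediately post-chemotherapy" to 1 year after baseline, and adds a 95% confidence interval. A parenthesis labels the start visit as both post-intervention and post-wait. One start visit and one end visit are fixed for both arms.

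The arms receive the programme at different times. In EX it runs alongside chemotherapy, "starting up to 1 week before participants’ chemotherapy start date and lasting approximately 12–24 weeks for those in the EX group". UC participants have usual care during chemotherapy and then "receive the ACTIVATE intervention for approximately 12 weeks following their last chemotherapy infusion". UC participants may be active on their own in the meantime: "No exercise restrictions are made".

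COGSUM is measured at baseline, at end of chemotherapy and at two later visits: "16-weeks post-chemotherapy (first follow-up), and at 1-year post-baseline (second follow-up)), participants complete a neuropsychological test battery". The self-report cognitive and quality-of-life questionnaires are completed at all five timepoints. MRI/fMRI and EEG are done only at baseline, end of chemotherapy and 1 year.

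**The concern.** Sustainability means keeping an effect after the intervention that produced it has ended. In UC the analysis starts before the intervention has been delivered, so there is nothing yet to sustain. The plan's own label for the start visit shows the mismatch: it is post-intervention for one arm and post-wait for the other.

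A UC gain caused by the delayed programme, by recovery after chemotherapy or by repeated testing would be reported under the name sustainability. Set beside the EX result, it would invite a comparison of two different quantities. This matters because the Discussion says the trial can help guide when exercise is given, and a UC gain reported as durability could feed into that reading.

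**Working it through.** The plan attaches no figure to this analysis, so there is none to reproduce. The check is a calendar and a short algebraic comparison.

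**1. Calendar.** Inputs: chemotherapy lasts L = 12 to 24 weeks (from the EX programme length) and is assumed to start near baseline; the UC programme lasts about 12 weeks and is assumed to start promptly after the last infusion; the first follow-up is 16 weeks after chemotherapy; 1 year is week 52.

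| Quantity | Formula | L = 12 | L = 24 |
|---|---|---|---|
| End of chemotherapy (start visit) | L | week 12 | week 24 |
| UC programme | L to L + 12 | weeks 12–24 | weeks 24–36 |
| 16-week visit | L + 16 | week 28 | week 40 |
| Planned window, either arm | 52 − L | 40 weeks | 28 weeks |
| Share of UC window taken by its programme | 12 / (52 − L) | 30% | 43% |
| UC window from the 16-week visit | 52 − (L + 16) | 24 weeks | 12 weeks |

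The 16-week visit falls 16 − 12 = about 4 weeks after the UC programme ends.

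**2. What the contrast measures.** Let g be the gain from the programme and k the fraction of it kept at 1 year. Set recovery and practice to zero for the moment.

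- EX starts at g and ends at kg, so its change is −g(1 − k).
- UC starts at 0 and ends at kg, so its change is +kg.
- The two differ by kg + g(1 − k) = g, whatever k is.

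Take g = 0.4 SD purely as an illustration. The document uses 0.4 SD only as a between-arm difference at end of chemotherapy and plans no such gain within UC.

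| Fraction kept (k) | EX change | UC change |
|---|---|---|
| 1 | 0 | +0.4 |
| 0.5 | −0.2 | +0.2 |
| 0 | −0.4 | 0 |

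Zero change is full maintenance in EX and complete loss in UC.

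**3. Recovery and practice.** Both add to the change in each arm. On practice, the article says alternate forms are unavailable for the two WAIS-IV tests, the word association test and Trail Making A and B: 5 of the 8 tests listed, counting Trail Making A and B separately. These terms affect EX too, but there the start visit is at least the right one.

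**4. Effect of moving the UC start.** If nothing is lost in the roughly 4 weeks before the 16-week visit, UC starts at g and its change becomes −g(1 − k), the same form as in EX.

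**The case against.** The strongest defence is that the UC estimate is not wrong. It validly describes how UC changed from the end of the wait to 1 year, and the label on the start visit shows that the authors knew it was post-wait for UC. Sustainability is also not among the stated objectives or hypotheses. The timing objective is answered by a separate between-arm contrast, the difference in change from baseline to 1 year. All of this stands, and it limits the weight of the point. It does not cure it: the text applies the name and the start visit to each group, and nothing elsewhere in the article gives UC a different start.

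A reader might infer three stronger claims, which the document does not support:

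- *That a non-significant loss will be declared sustained.* No such decision rule is written, and a 95% confidence interval is planned. A tolerance margin is detail that an article may leave to the full plan.
- *That UC has done no exercise by the start visit.* Self-directed activity is unrestricted. What UC has not received is the ACTIVATE programme.
- *That the error can be sized by the power to detect a planned 0.4 SD gain in UC.* No such gain is planned, and the stated correlation of 0.8 is with baseline, not between the two later visits.

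The remedy also has limits, set out under the fix.

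**Conclusion.** The point holds for UC. As written, the UC sustainability contrast runs from before the programme to 1 year and does not measure maintenance. On the calendar assumptions above, 30–43% of its window is the programme itself. In the simplified case without recovery or practice, it is displaced from the maintenance quantity by the full programme gain g; the size of g is unknown.

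It should be fixed before analysis but is not critical. The EX start visit is appropriate, and the primary comparison at end of chemotherapy, the sample size and the between-arm 1-year timing contrast do not depend on it. A reader might suppose that the timing question is compromised; it is not, because it rests on the separate randomised contrast.

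**What to change.** **COGSUM and the questionnaires.** Keep end of chemotherapy to 1 year for EX. Define UC sustainability as change from the 16-week post-chemotherapy visit to 1 year, and include that visit in the repeated-measures model. Report the UC change from end of chemotherapy to 16 weeks separately, as an uncontrolled pre-post change that includes recovery and practice.

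**MRI/fMRI and EEG.** With no 16-week assessment, the start cannot be moved. If the analysis is applied to these outcomes, call the UC contrast change over the delayed-exercise and follow-up period, not sustainability.

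**State with the results:**

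- The windows after the programme differ: about 28–40 weeks in EX and 12–24 weeks in UC, assuming chemotherapy of 12–24 weeks starting near baseline. The two changes are not directly comparable.
- Loss in the roughly 4 weeks between the end of the UC programme and the 16-week visit is not captured.
- The 4-week gap assumes a prompt start and a 12-week programme. If the two together overrun by more than 4 weeks, the visit falls inside the programme, so actual end dates should be checked.

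The cost is a paragraph of analysis wording. No new visit, test or participant is needed, since COGSUM and the questionnaires are already collected at 16 weeks.
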